## Abstract

**Background:**

Overweight and obese women show reduced conception rates compared to women of normal weight. Insulin resistance and increased amount of visceral fat may be important mechanisms for reduced fertility in these women. Exercise training, in particular with high intensity, has previously been found to improve insulin sensitivity in overweight subjects. This study will assess if regular high-intensity interval training will improve the pregnancy rate after assisted fertilization compared to usual care only in overweight and obese women. We hypothesize that the intervention will improve pregnancy rate and insulin sensitivity compared to the control group.

**Methods/design:**

The FertilEX study is a randomized, controlled trial in which 140 women with body mass index (BMI) >25 kg/m^2^ accepted for assisted fertilization will be randomized (1:1) to an intervention group or a control group. The intervention group will do high-intensity interval training three times per week for 10 weeks before assisted fertilization. The control group will receive standard care assisted fertilization only. The primary outcome measure is ongoing pregnancy 7–8 weeks after embryo transfer. Secondary outcome measures are insulin sensitivity, peak oxygen uptake, brachial flow-mediated endothelial function, levels of reproductive hormones, and body composition.

**Discussion:**

The results of this trial will provide knowledge about the effects of high-intensity exercise before assisted fertilization in subfertile overweight/obese women. If the intervention leads to beneficial effects on outcome measures, such programs should be considered as part of regular fertility care procedures for this population of women.

**Trial registration:**

ClinicalTrials.gov: NCT01933633. Registered on 28 August 2013.

**Electronic supplementary material:**

The online version of this article (doi:10.1186/s13063-016-1398-x) contains supplementary material, which is available to authorized users.

## Background

Obesity prevalence is increasing among women of reproductive age. This has evident consequences for public health, as obesity is associated with several chronic diseases and premature mortality [1, 2]. In addition, obesity is associated with an increased risk of subfertility [3]. Women who have a body mass index (BMI, in kg/m^2^) above 24 have a significantly elevated relative risk of subfertility compared to women with lower BMIs [4]. Although the exact mechanism through which fertility is affected by body mass and body fat is uncertain, adipose tissue has been shown to disturb the secretion and bioavailability of sex hormones and to affect egg quality, via effects of insulin, leptin, and adipokines [5, 6]. In addition to obesity alone, polycystic ovary syndrome (PCOS) is a common endocrine disorder affecting 6–20 % of women of reproductive age [7] and is currently recognized as the leading cause of anovulatory infertility.

The mechanisms underlying the intrinsic insulin resistance in PCOS remain unclear, but potentially they are associated with increased abdominal visceral fat [8]. In other insulin resistant populations, exercise training has consistently been shown to improve cardiovascular risk factors and reduce the risk of type 2 diabetes [9–11]. Furthermore, insulin sensitivity has been found to increase after a period of exercise training [10, 12]. Sim et al. [13] found significantly improved pregnancy rates after a 12-week weight loss program including exercise advice and diet intervention in obese women undergoing assisted fertilization. A recent observational study [14] also indicated that regular physical activity is associated with improved fertility in obese women going through fresh in vitro fertilization (IVF) or intracytoplasmic sperm injection (ICSI) cycles. Still, there is a considerable gap in the research literature regarding the effects of exercise training on fertility outcomes, and future research should focus on well-designed, adequately powered studies to address this gap [15]. In particular, research is needed on the isolated effects of exercise training, i.e., in the absence of dietary interventions. Also, there is a great need to understand the potential mechanisms through which exercise training can affect fertility.

In this article, we describe the design and methods of the FertilEX trial, a randomized controlled trial of exercise training prior to assisted fertilization in overweight and obese women.

The primary aim of the FertilEX trial is to test the hypothesis that overweight and obese women who exercise regularly prior to assisted fertilization will improve their pregnancy rate compared to women who only receive usual care assisted fertilization. The FertilEX trial will investigate possible mechanisms for increased fertility after exercising, such as insulin sensitivity, body composition and fat distribution, secretion and bioavailability of sex hormones, egg quality, cytokine levels, and blood markers of low-grade inflammation. Furthermore, we will assess the effects of exercise training on peak oxygen uptake, peripheral arterial endothelial function, and blood pressure.

## Methods

### Objectives

Our main hypothesis is that high-intensity interval training (HIT) before going into regular assisted fertilization with IVF or ICSI will improve the pregnancy rate in overweight and obese women. As a mechanistic explanation of the increased pregnancy rate, we expect that insulin sensitivity will improve in the women in the exercise group, and that the amount of reproductive and metabolic hormones will change towards normal values in these women.

### Participants and setting

The trial is conducted at St. Olavs Hospital, Trondheim University Hospital in collaboration with the Norwegian University of Science and Technology (NTNU), Trondheim, Norway. The trial includes women with a BMI >25 kg/m^2^ who are accepted for assisted fertilization at the St. Olavs Hospital. The trial was designed following the Standard Protocol Items: Recommendations for Interventional Trials (SPIRIT) 2013 statement (see Additional file 1).

Inclusion and exclusion criteria are listed in Table 1. To be included, the women must be willing to come to Trondheim for baseline assessments and post-testing after the intervention period. If allocated to the intervention group, the women must be willing to attend supervised training until they are familiarized with the training protocols and to continue to do HIT for 10 weeks.

**Table 1 Tab1:** Inclusion and exclusion criteria

Inclusion criteria	Exclusion criteria
Age ≥18 years	Current high-intensity exercise training ≥2 times per week
Accepted for assisted fertilization	Current or previous Metformin® use (with wash-out period of >4 weeks)
BMI >25 kg/m^2^	Physical impairments limiting exercise training
Able to come for assessments at baseline and follow-up	Unable to follow verbal and written instructions in Norwegian or English
	Unwilling to suspend fertility treatment for 10 weeks

The recruitment started in November 2013 and will continue until the needed number of participants is included, anticipated until the end of 2018. Participating women in the training group get a free membership at a local gym during the intervention period, and women in the control group get a gift from the gym worth $85 US dollars.

### Randomization and allocation

Participants are stratified for PCOS (yes/no) and randomly assigned to either the intervention or control group after initial assessments in a 1:1 manner, as outlined in the flow diagram (Fig. 1). Randomization is performed by a web-based randomization system developed and administered by the Unit of Applied Clinical Research, Institute of Cancer Research and Molecular Medicine, NTNU, Trondheim, Norway. The randomization is in blocks with varying block size.

**Fig. 1 Fig1:**
[figure not shown]
Participant flow through the FertilEX study

### Intervention

The exercise training program consists of HIT performed three times per week for 10 weeks. In two of the weekly sessions, the participants perform intervals with an intensity of 85–95 % of individual heart rate maximum for 4 minutes, repeated four times (Fig. 2a). In the third weekly exercise session, they perform intervals with maximum intensity that can be sustained for 1 minute, repeated 10 times (10 × 1) (Fig. 2b). All exercise training is preferably done as treadmill walking or running. In case of trouble with walking on a treadmill, other forms of exercise (bicycle, etc.) are used. This exercise regime has previously been found to improve insulin resistance by 17 % in women with PCOS [16]. The participants attend supervised exercise sessions until they are familiar with the training protocols. Thereafter, they continue exercising at the hospital or at a local gym. The participants wear heart rate monitors (Polar RCX3, POLAR, Oulu, Finland) at all training sessions to ensure that the exercise intensity is as prescribed. Heart rate data will be stored in a personal online training diary (http://www.polar.com) for use in analyses of compliance and exercise intensity. Exercise intensity is checked regularly throughout the intervention period by the study personnel. After the 10-week initial training period, all women follow standard care assisted fertilization, as described in the next paragraph. They are also encouraged to exercise as described above in the weeks of the fertility treatment until ovulation induction. Thus, the total exercise period is 13–15 weeks, depending on the fertility treatment protocol chosen by the treating physician. Women in the control group receive regular advice from the hospital staff about physical activity (usual care).

**Fig. 2 Fig2:**
[figure not shown]
Training protocols. **a**) 4 × 4 min interval training. **b**) 10 × 1 min interval training

The fertility treatment includes an ovarian stimulation protocol, which is individualized for each patient according to standardized routines at the Fertility Unit, St. Olavs Hospital. We assume that the different protocols will be equally distributed in the interventional and control groups. The treatment includes either a short or a long stimulation protocol. The selection of protocol is done by the treating physician, who is blinded for group allocation. The treatment usually starts with a spontaneous onset of the period or by the use of progestins for women with long intervals between their menstrual bleedings. Prior to ovarian stimulation with gonadotropins, a urine hCG test to exclude pregnancy is taken by the patients at home. For the short ovarian stimulation protocol, one out of the three gonadotropins (Puregon®, Gonal-F®, or Menopur®) is administrated daily from cycle day 2 or 3. The antagonist (Orgalutran® 0.25 s.c.) is administered from the 5th treatment day. In the long gonadotropin releasing hormone (GnRH) agonist protocol, pituitary suppression is initiated with 800 μg nafarelin (Synarela® nasal spray) 5–7 days before the estimated start of the next menstrual bleeding and continued until the end of gonadotropin administration. Gonadotropin treatment starts after at least 14 days on GnRH agonist downregulation. Ovulation is induced by hCG injection (Ovitrelle 250 μg s.c.) when at least three follicles measure >17 mm. Ovum pick up is performed transvaginally 36 h later. The method used for fertilization is either IVF or ICSI. The day of embryo replacement is day 2, 3, or 5 after oocyte retrieval. Luteal phase support is given for 2 weeks. The patients take a urine hCG test 14 days after embryo replacement. For patients with a positive pregnancy test, a vaginal ultrasound examination is performed by 7 to 8 weeks of gestation.

### Study assessment visits

Participants come for research visits at baseline and after the intervention period (10 weeks) (Fig. 1). Clinical data collected by the hospital recordings during the treatment will be available for the study investigators.

### Outcome measures

The primary outcome measure is ongoing pregnancy, defined as the sonographic evidence of intrauterine gestational sac and fetal heart activity at 7 to 8 weeks of gestation. If not pregnant, the women will either do another IVF/ICSI cycle or are evaluated as not suitable for further treatment cycles, based on the treating physician’s decision. They will be considered as a negative for the primary outcome if not pregnant after the initial cycle.

Secondary outcome measures are insulin sensitivity, levels of reproduction-related hormones (luteinizing hormone (LH), follicle-stimulating hormone (FSH), prolactin, anti-Müllerian hormone (AMH), testosterone, free androgen index (FAI), sex hormone-binding globulin (SHBG)), peak oxygen uptake, brachial flow-mediated endothelial function, body weight, body composition, quality of life, physical activity, and diet. Also, the Fertility Unit systematically registers the number of eggs retrieved, the proportion of fertilized eggs and embryo quality, and pregnancy outcome data. These data will be available for the study investigators.

We measure insulin sensitivity by the gold standard, the hyperinsulinemic-euglycemic clamp, using a modification of the method originally described by De Fronzo et al. [17]. The subjects are placed in an adjustable bed in the supine position in a quiet and temperature stable room. Catheters are inserted in the right and left antecubital veins. The left catheter is used for blood sampling and the right for infusion of insulin and glucose. The left arm is placed in a heat package to enhance flow. Initial samples are collected to determine fasting glucose and insulin concentrations. After 30 min rest, human insulin (Actrapid®, Novo Nordisk, Bagsvaerd, Denmark), diluted in 500 mL NaCl 0.9 % to 300 mU/mL, is infused at a rate of 40 mU/m^2^/min, and maintained for the entire test. Plasma glucose concentration is measured every 5th minute (EKF Biosen C-line Sport, EKF diagnostic GmbH, Barleben, Germany) and kept at about 5.0 mmol/L for at least 30 min by adjusted infusion of 20 % glucose. Blood samples for assessing plasma insulin are taken at 30, 60, 90, and 120 min, as well as every 10th minute during the last 30 min of the test. The steady-state glucose infusion rate (GIR) is calculated for the last 30 min of the test, and the average GIR during this period will be used as the measure of insulin sensitivity. The homeostasis model assessment of insulin resistance (HOMA-IR) [18] will also be calculated.

Blood samples are obtained in the morning after a ≥10 h overnight fast and will be analyzed for concentrations of lipids, glucose, hemoglobin, glycated hemoglobin (HbA1c), albumin, high-sensitive C-reactive protein (CRP), and insulin C-peptide. The hormone assays include the evaluation of the above-mentioned reproduction-related hormones, as well as insulin, thyroid-stimulating hormone, leptin, and adiponectin. All analyses are conducted according to standard procedures at the Department of Medical Biochemistry, St. Olavs Hospital. Biological materials are stored at the Regional Biobank of Central Norway. Blood and urine samples are also collected and stored at the Regional Biobank of Central Norway for later analyses not yet planned. The Biobank is approved by the Data Inspectorate of Norway and by the Regional Committee for Medical Research Ethics. All information in the Biobank is handled according to the guidelines of the Data Inspectorate. Samples are stored with a unique identity number, corresponding to the participant’s identity number in the study, and with data on what the sample contains and when it was taken.

Peak oxygen uptake is measured in an incremental test to exhaustion by a direct ergospirometry system with a mixing chamber (Oxygen Pro, Erich Jaeger GmbH, Hoechberg, Germany) on a treadmill (Woodway USA Inc., Waukesha, WI, USA). A leveling off of oxygen uptake despite increased workload and a respiratory exchange ratio ≥1.05 are used as criteria for peak oxygen uptake. Measurements of peak oxygen uptake are performed at the core facility NeXt Move, Norwegian University of Science and Technology (NTNU).

Brachial flow-mediated endothelial function is measured by high-resolution vascular ultrasound (14 MHz Doppler probe, Vivid 7, GE Vingmed Ultrasound AS, Horten, Norway) according to current guidelines [19, 20]. The subjects are asked to refrain from strenuous physical activity for ≥48 h before the assessments, and measurements are obtained after a ≥10 h overnight fast. Measurements are conducted in a quiet and temperature stable room (22–24 °C) after 20 min of rest in a supine position. Baseline images are taken before occluding the forearm’s distal part by inflation of a pneumatic cuff (SC10, D.E. Hokanson, Inc., Bellevue, WA, USA) to 250 mmHg for 5 min. A longitudinal image of arterial diameter and pulse wave velocity signals is recorded continuously for 3 min after cuff release. An integrated electrocardiogram (ECG) is used to assess the diameter according to the cardiac cycle.

Body weight, fat mass, and fat-free mass are measured using bioelectrical impedance analysis (InBody 720, Biospace CO, Ltd., Seoul, Korea). Additionally, waist circumference is measured at the level of the umbilicus to further estimate the distribution of body fat.

Psychological well-being and quality of life are measured using standardized questionnaires, the Psychological General Well-Being Inventory [21] and the generic SF-36 quality of life questionnaire [22], respectively.

Physical activity is registered by questionnaires and by activity monitors (SenseWear, BodyMedia, Inc., Pittsburgh, PA, USA) at baseline and after 10 weeks. The subjects wear the activity monitor for five days: three weekdays and two weekend days. Diet is registered by an electronic standardized food frequency registration system [23] for two weekdays and one weekend day.

### Power calculation and statistical analyses

A clinical pregnancy rate of 0.30 during the first treatment cycle can be expected in this patient group. As the research hypothesis of this study is original, we have little previous data to support the power calculation. Based on a previous pilot study on giving advice about exercise and diet to improve pregnancy rates [24], we expect that the pregnancy rate in the intervention group will be increased to 0.55. With a statistical power of 0.80 and a significance level of 0.05, it is estimated that 61 patients are needed in each group to demonstrate the increased pregnancy rate. To allow for an expected 15 % dropout, we will include 140 participants in the study. We will analyze the data using the intention-to-treat principle (main analysis). Since dropout is one of the main concerns in studies of lifestyle modifications, we will also analyze the data with a per protocol analysis, excluding women in the intervention group who did not follow the prescribed intervention (defined as attending less than 80 % of the exercise sessions). As women in the control group might start exercising on their own, in the per protocol analyses we will exclude women in that group reporting to do high-intensity endurance training (making them breathe heavily) twice weekly or more during the intervention period. The proportion of women with ongoing pregnancy in the intervention and control groups will be compared using stratified (for PCOS/not PCOS) analysis of 2 × 2 tables. Missing data regarding pregnancy and fertilization outcome will be imputed with a negative result or zero; i.e., if no oocytes are collected during the assisted fertilization, the fertilization rate will be regarded as missing. The null hypothesis is that the proportion is equal in both groups, while the alternative hypothesis is that the proportion is larger in the intervention group. Secondary outcomes will be analyzed using analysis of covariance (ANCOVA), as suggested by Vickers and Altman [25]. We will use intervention group (exercise/control) as a fixed factor in the analyses and the baseline value of each outcome measure and PCOS status (PCOS/not PCOS) as covariates. When data on secondary outcomes are missing, we will use multiple imputation if we can assume that the data are missing at random. If we assume that the data are not missing at random, we will analyze only available data.

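### The 140-woman sample size allows for dropouts as if they were excluded, but the main analysis keeps them; with 15% dropout, power is about 73–75%, not 80%

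*Protocol article*

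**What the plan says.** All of the following stands in the protocol article under Power calculation and statistical analyses.

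- Assumed rates: "A clinical pregnancy rate of 0.30 during the first treatment cycle can be expected in this patient group", and "we expect that the pregnancy rate in the intervention group will be increased to 0.55".
- Size, for 80% power at the 0.05 level: "it is estimated that 61 patients are needed in each group to demonstrate the increased pregnancy rate".
- Allowance for dropout: "To allow for an expected 15 % dropout, we will include 140 participants in the study".
- Main analysis: intention to treat, with a per-protocol analysis as an addition.
- Missing primary outcome: "Missing data regarding pregnancy and fertilization outcome will be imputed with a negative result or zero".
- Direction of the test: "the alternative hypothesis is that the proportion is larger in the intervention group".

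Two other sections matter. Study assessment visits and Outcome measures say that the hospital's clinical data, including pregnancy outcomes registered by the Fertility Unit, will be available to the investigators. Outcome measures also limits the primary outcome to the first treatment cycle.

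**The concern.** Going from 122 to 140 suits an analysis of completers: some women disappear, and those who remain still have rates of 0.30 and 0.55. The specified main analysis works differently. A woman who drops out stays in the denominator of her arm. If her outcome is unknown she counts as not pregnant, which lowers the rate in her arm. If her outcome is known but she stopped training, she may not have the benefit assumed for the intervention arm. Either way the expected difference is smaller than the 25 points used for the sample size, and the assumed rates were not lowered for this.

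The stake is the chance of missing a real effect. The article itself says that few data support the power calculation and that dropout is a main worry in lifestyle trials, so there is little margin to spend on an allowance that does not match the analysis.

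**Working it through.** **Inputs.** Rates 0.30 and 0.55, two-sided alpha 0.05 (z = 1.960), power 0.80 (z = 0.842), 15% dropout, 140 women allocated 1:1 and so 70 per arm. All are from the power section except the allocation ratio (Randomization and allocation) and the two-sided reading, which step 1 supports.

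**1. Reproduce the plan's figure.** With p̄ the mean of the two rates, the pooled-variance formula without continuity correction is

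n = [1.960·√(2p̄(1−p̄)) + 0.842·√(p1(1−p1) + p2(1−p2))]² / (p2−p1)²

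With p̄ = 0.425, n = [1.960 × 0.6991 + 0.842 × 0.6764]² / 0.0625 = 60.2, rounded up to 61. This matches. The other conventions tried do not: one-sided 48, two-sided with continuity correction 68, two-sided unpooled 58, two-sided arcsine 60. The sample size was therefore evidently computed two-sided.

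**2. Power formula.**

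Power = Φ( [√n·(p2−p1) − 1.960·√(2p̄(1−p̄))] / √(p1(1−p1) + p2(1−p2)) )

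**3. Reading A: every dropout lacks an outcome, 15% in each arm.**
- Rates: 0.30 × 0.85 = 0.255 and 0.55 × 0.85 = 0.4675; difference 0.2125; p̄ = 0.36125.
- Power = Φ([8.367 × 0.2125 − 1.960 × 0.6793] / 0.6625) = Φ(0.674) = 75.0%. Exact binomial enumeration of the same test also gives 75.0%.

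**4. Reading B: 15% of the intervention arm stop training, all outcomes are known, and these women conceive at the control rate.**
- Rates: 0.30 and 0.85 × 0.55 + 0.15 × 0.30 = 0.5125; difference again 0.2125; p̄ = 0.40625.
- Power = Φ([8.367 × 0.2125 − 1.960 × 0.6946] / 0.6781) = Φ(0.614) = 73.0%.

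**5. Other cases, 70 per arm unless stated, two-sided 0.05.**

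| Assumption | Rates | Power |
|---|---|---|
| No outcome lost and full benefit kept | 0.30 v 0.55 | 85.7% |
| Dropouts excluded (59.5 per arm) | 0.30 v 0.55 | 79.5% |
| 10% of each arm missing, set to negative | 0.27 v 0.495 | 78.8% |
| 20% of each arm missing, set to negative | 0.24 v 0.44 | 70.9% |
| 7.5% of each arm missing, other dropouts keep planned rates | 0.2775 v 0.50875 | 80.7% |
| 15% missing in the intervention arm only | 0.30 v 0.4675 | 53.1% |

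The second row is the case that the inflation to 140 serves: it gives almost exactly the planned power. The other rows keep all randomised women, as the main analysis does.

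**The case against.** **Dropout need not mean a missing outcome.** The article mentions dropout again as the reason for a per-protocol analysis based on attendance, which concerns adherence. Hospital records can supply the pregnancy result of a woman who stopped training. This stands, and it makes the 75% conditional: if only half of the dropouts lack an outcome and the others keep the planned rates, power is 80.7%. It does not remove the point, because known outcomes help only as far as women who stop training still benefit. If they conceive at the control rate, power is 73%.

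**A reader might infer that 15% dropout, negative imputation and 80% power cannot all hold at 140 women.** The documents do not support that. The alternative is worded in one direction, and a one-sided 0.05 test gives 84% under reading A. However, a one-sided calculation would have needed 48 per group, not 61, so the plan's own size is not on that basis.

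**A reader might infer that retrieving clinic records brings power towards 86%.** That needs women who stop training to conceive at the full 0.55, which nothing in the article supports.

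**A reader might infer that 140 is itself a miscalculation, because 122/0.85 = 144.** This is immaterial: 122 × 1.15 = 140.3, and excluding dropouts from 140 still gives 79.5%.

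**The loss is modest.** It is 5 to 7 points in the two main readings. That is fair, and it limits the weight of the point.

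**Conclusion.** The point holds in conditional form. The dropout allowance is built for an analysis that excludes dropouts, while the specified main analysis keeps them. At 140 women and 15% dropout, two-sided 0.05, power is about 75% when all dropouts lack an outcome equally in both arms, and about 73% when those leaving the intervention have known outcomes at the control rate. The type II error is then 25–27% instead of the planned 20%.

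These figures rest on the plan's own 0.30 and 0.55, on the two-sided basis that reproduces 61 per group, and on an unstratified calculation; the planned test is stratified for PCOS, and the article gives no stratum rates. Milder dropout or a retained training benefit would bring power to 80% or above. Loss confined to the intervention arm would take it well below 73%.

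**What to change.** 1. Restate the power for the specified analysis: about 73–75% with 140 women, 15% dropout and two-sided 0.05. Say which assumption about dropouts each figure carries (no outcome and counted as not pregnant, or known outcome at the control rate).
2. State that leaving the training programme is not a missing primary outcome. The first-cycle result is taken from clinic records for every randomised woman, and negative imputation applies only where no such record exists. This should not be presented as a gain in power.
3. State the sidedness of the primary test, so that the worded alternative and the sample size agree.

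The cost is a less favourable power figure and a few sentences. The article describes access to records at the hospital's Fertility Unit; for the second fertility centre added in February 2016 (Trial status and change in study protocol after trial initiation) it does not say so, and access there needs to be confirmed. No extra patients are needed to restate the figure. If the sponsor prefers to restore 80% under reading A, the step 1 formula with 0.255 and 0.4675 gives 79.03, so 80 per arm or 160 in total. With 16 women included by March 2016, either choice was still open when the article was written.

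### As written, the secondary per-protocol analysis excludes early leavers from the exercise arm but keeps control leavers without an outcome as not pregnant

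*Protocol article*

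**What the plan says.** All the relevant rules are in the protocol article, section Power calculation and statistical analyses. Intention-to-treat is named as the main analysis. A per-protocol analysis is added, with dropout as its reason: "Since dropout is one of the main concerns in studies of lifestyle modifications, we will also analyze the data with a per protocol analysis".

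The per-protocol set is defined separately for each arm:

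- **Exercise arm:** "excluding women in the intervention group who did not follow the prescribed intervention", with the threshold at 80 % of sessions.
- **Control arm:** women are removed only if they report high-intensity endurance training at least twice a week during the intervention period.

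After both analyses have been described, the section gives one rule for missing outcomes: "Missing data regarding pregnancy and fertilization outcome will be imputed with a negative result or zero". It is not tied to either analysis set.

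**The concern.** Each rule is understandable alone, but together they treat the same event differently by arm. A woman who leaves the exercise arm early in training cannot reach 80 % attendance, so she is dropped from numerator and denominator. No rule removes a control woman who leaves. If she reports nothing she cannot meet the control exclusion, and if she has no recorded pregnancy outcome she is counted as a failure.

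The intention-to-treat analysis does not have this problem, because leavers without an outcome are negative in both arms. The asymmetry arises only in the analysis that was added to deal with dropout. Readers often take a per-protocol result as the effect in women who actually trained, so a difference produced by coding could be mistaken for such an effect.

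**Working it through.** **Inputs from the protocol article**

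- Pregnancy rate without an effect: "A clinical pregnancy rate of 0.30 during the first treatment cycle can be expected in this patient group".
- Design rate with exercise, 0.55: "we expect that the pregnancy rate in the intervention group will be increased to 0.55".
- Sample size: "With a statistical power of 0.80 and a significance level of 0.05, it is estimated that 61 patients are needed in each group".
- Dropout and total: "To allow for an expected 15 % dropout, we will include 140 participants in the study". With 1:1 allocation this is 70 per arm.
- Direction of the alternative: "the alternative hypothesis is that the proportion is larger in the intervention group".

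**The plan's own figure.** The pooled-variance formula for two proportions, without continuity correction, uses a mean rate of (0.30 + 0.55)/2 = 0.425:

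n = [1.960 × √(2 × 0.425 × 0.575) + 0.842 × √(0.30 × 0.70 + 0.55 × 0.45)]² / 0.25² = 60.2, rounded up to 61.

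This matches the stated 61. A one-sided 0.05 test would give 48, so the trial was sized on a two-sided test although the alternative is worded in one direction. Error rates are therefore given on both bases.

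**Bias under no effect.** Let m be the share of controls whose pregnancy outcome is missing. Suppose that all exercise leavers go before 80 % attendance.

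- Exercise rate in the per-protocol set: 0.30.
- Control rate in the per-protocol set: 0.30 × (1 − m).
- Spurious difference: 0.30 − 0.30 × (1 − m) = 0.30 × m.

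The exercise arm is taken as 70 × 0.85 = 59.5, about 60 women, and the control arm as 70. The probabilities of a finding in favour of exercise come from exact binomial enumeration of the unstratified pooled z-test. Apart from 15 %, the values of m are assumptions.

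| m | Control rate | Spurious difference | One-sided 0.05 | Favourable tail, two-sided 0.05 |
|---|---|---|---|---|
| 0 % | 0.300 | 0 points | 5.1 % | 2.2 % |
| 5 % | 0.285 | 1.5 points | 7.5 % | 3.4 % |
| 10 % | 0.270 | 3.0 points | 10.6 % | 5.2 % |
| 15 % | 0.255 | 4.5 points | 14.6 % | 7.6 % |

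If 15 % of controls leave but the clinic still holds outcomes for half of them, m = 7.5 % and the difference is 0.30 × 0.075 = 2.25 points.

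**Offset from late exercise leavers.** Exercise women who reach 80 % attendance and then leave without an outcome stay in as negatives. As an illustration, assume that 10 of 70 exercise women leave, 5 early and 5 late. The set then holds 65 women, 60 of them with an outcome, and the exercise rate is 0.30 × 60/65 = 0.277.

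- m = 15 %: 0.277 − 0.255 = +2.2 points (8.7 % one-sided).
- m = 5 %: 0.277 − 0.285 = −0.8 points (3.9 % one-sided), now against exercise.

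**With the design effect.** If women who stay become pregnant at 0.55 and 0.30, then m = 15 % with all exercise leavers early gives 0.55 − 0.255 = 29.5 points instead of 25.

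**With one rule in both arms.** Excluding leavers from both arms (60 against 60, both at 0.30) gives an expected difference of 0 and a one-sided error of 5.1 %.

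**The case against.** Several points on the other side are sound.

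- **The missing-outcome rule is not expressly applied to the per-protocol set.** That is so, and a fuller document might restrict it. But the article states the rule without restriction, after describing both analyses, so following the text produces the asymmetry.
- **The 15 % is not a rate of missing control outcomes.** It is an overall allowance used to enlarge the sample. Under Study assessment visits and Outcome measures, clinical and pregnancy data come from clinic records, so a woman who misses a study visit can still have a known outcome. Under Trial status, controls no longer wait 10 weeks from February 2016. Only 16 women had been included by March 2016, so at least 124 of 140 (89 %) enter under the changed design. This stands and makes 15 % an upper scenario. It does not guarantee zero: a woman who never starts treatment has no cycle to record, and the plan itself provides for missing pregnancy outcomes.
- **The direction is not certain.** A reader might infer that the rules always manufacture a benefit of exercise. They do not: enough late exercise leavers can cancel or reverse the shift, as the illustration shows.
- **The analysis is secondary.** A reader might also infer that the plan lets a per-protocol result rescue a null trial. Nothing in the document allows this, since intention-to-treat is explicitly the main analysis.

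**Conclusion.** The point holds in a limited form. The written per-protocol rules handle leavers differently by arm, and the resulting bias is 0.30 times the share of controls with missing outcomes, less the offset from late exercise leavers. Without that offset it runs from nothing, if every control outcome is recorded, to 4.5 points. The top figure needs three things at once: the full dropout allowance applies to controls, all those outcomes are missing, and every exercise leaver goes early. The document's own arrangements make the low end more likely.

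The figures assume that women who stay become pregnant at 0.30 in both arms, and that the unstratified test approximates the planned stratified one. They leave out the separate bias from selecting women who adhere. The main analysis is untouched. The point is worth correcting because the rules conflict as stated and the correction is cheap, not because a large distortion is expected.

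**What to change.** State one rule for women with missing pregnancy outcomes that applies identically to both per-protocol arms. For example: the per-protocol comparison includes only women with an observed first-cycle pregnancy outcome, any pregnancy recorded before the cycle starts counts as observed, and missing outcomes are not set to negative in this set. The clause on earlier pregnancies prevents the loss of a woman who conceives during the training period, which most controls no longer have as a waiting period. The missing-as-negative rule can stay as it is for the intention-to-treat analysis.

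The cost is one sentence and a slightly smaller per-protocol control group, with no new data. The change does not make the comparison a randomised one: it still conditions on adherence and on reaching an observed outcome, both of which follow randomisation. It should continue to be reported as supportive to intention-to-treat, with the number of missing outcomes shown by arm.
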